#### Tissue and Serum Banking:

#### All patients will have a 15 ml red top drawn at enrollment, at two weeks and at the completion of soy supplementation. From this, we will use a 1ml aliquot for genistein analysis and a 1ml aliquot IGF-1/IGFBP-3 analysis. The remaining sample will be labeled and stored in –700C. Our studies will also require one tissue core of tumor and adjacent normal tissue. When feasible, at least one additional core of both tumor and normal tissue will be collected according to the tissue collection methods listed above. Samples will then be labeled and stored in liquid nitrogen. These samples will be available for additional investigation including potential future collaborative efforts. The KCVA is also one of the sites selected for the planned VA tissue and biorepository project and these samples could readily be contributed to that tissue bank.

####

1. PATIENT ACCRUAL

Patients will be accrued at the Kansas City Veterans Affairs medical center (KCVA). The Kansas City VAMC is the tertiary referral center for the western orbit of VISN 15 and serves a large veteran population. Patients from the Leavenworth and Topeka VAMC’s who desire prostatectomy for treatment of their prostate cancer are also referred to the Kansas City VA’s urologic surgeons, [name] and [name]. Each year 100-120 new cases of prostate cancer are diagnosed, the majority of which are early stage, with an average 40-50 prostatectomies performed yearly. The majority of the remaining patients are treated with either external beam radiation therapy, brachytherapy or hormonal therapy. In the pilot study that was performed at the KCVA alone, 13 patients were enrolled in less than six months, with nine of the patients being enrolled in a three-month time period. Patient acceptance approached 100%, given the low toxicity and ease of administration of the treatment intervention.

### STATISTICAL PLAN:

The primary objective of this study is to evaluate the molecular effects of soy isoflavones on human prostate cancer as well as the effects on serum androgen and estrogen levels. The goal is to randomize a total of 86 patients (43 to the control/placebo arm and 43 to the treatment/240mg soy arm). We will use a placebo and the lab personnel as well as clinicians, nurses and study coordinators will be blinded to treatment arm.

Randomization

Patients will be sequentially randomized into one of the two arms. Random permuted block randomization will be utilized. An independent statistician will generate the codes and will provide a copy of them to the VA research pharmacy. The study coordinator will notify the research pharmacy of the subjects ID number and the pharmacy will prepare the medication and distribute it to the patient.

Data Management

Two versions of an Access database will be created that mimics the patient data collection forms. One will be called primary and the other verification. Data will be entered into each database and then compares will be run to ensure the number of patients in each database is identical and that each data item is identical. This will be done each time data is to be entered. Logic, edit and range checks will be performed after compares have shown that the data in the primary and verification databases are identical. After the final patients data have been entered, compared and all logic, edit and range checks have been complete the database will be locked and data analysis will begin.

Sample Size and Power

Two primary endpoints for specific aim 1 are total serum estrogen and testosterone. The goal is to determine if there is a difference in the change in these values between the two groups. Each of these endpoints will be tested at the 0.025 level of significance. Data from the pilot study indicated that total serum estrogen reductions will be 0 and 47 in the control and treatment arm respectively, with a common standard deviation of 36. From the same pilot study we expect that serum testosterone reduction will be 0 and 1.36 for the control and treatment arm respectively, with a common standard deviation of 2. Given this information, we want a sufficient sample size to have at least 80% power to detect these changes for both endpoints at the 0.025 level of significance. Using a two-sample t-test, 43 subjects per group will give us over 95% power to detect the expected difference in estrogen and 80% power to detect the expected difference in testosterone.

Statistical Analysis Plan:

Categorical demographic variables and baseline characteristics will be summarized by frequencies and percentages, overall and by group. Quantitative demographic variables and baseline characteristics will be summarized by means and standard deviations, overall and by group. For specific aim 1, the primary endpoints are total estrogen and testosterone. We will summarize baseline, post-treatment and change for these variables by means and standard deviations for both groups. We will then compare the change in each of these endpoints using a two-sample t-test, at the 0.025 level of significance. Similar procedures will be done on the other serum endpoints; estradiol, PSA, 5-DHT, IGF-1, and IGFBP-3, however, these tests will be at the 0.05 level of significance.

In an exploratory manner, we will use general linear models to determine if some or any of the baseline characteristics are predictive of change in these variables while controlling for treatment. We will also use Pearson’s correlation to determine if changes in the biomarkers are correlated with one another. For specific aim 2, the primary endpoints are ER-α and ER-β. Similar analyses to what was used for specific aim 1 will be applied to these endpoints as well at the 0.05 level of significance.

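### The fixed 0.025/0.025 split for total estrogen and testosterone is valid, but Holm's procedure would add up to about 7 points of testosterone power at the same familywise error

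*Protocol*

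**What the plan says.** The Sample Size and Power text of the Statistical Plan names the family: "Two primary endpoints for specific aim 1 are total serum estrogen and testosterone". It then fixes the level: "Each of these endpoints will be tested at the 0.025 level of significance". The Statistical Analysis Plan text under the same heading repeats it: "We will then compare the change in each of these endpoints using a two-sample t-test, at the 0.025 level of significance". Neither place describes a step-down rule, a hierarchy, or any passing of unused significance level from one endpoint to the other.

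The planning values come from a pilot. For estrogen, "total serum estrogen reductions will be 0 and 47 in the control and treatment arm respectively, with a common standard deviation of 36". For testosterone, "serum testosterone reduction will be 0 and 1.36 for the control and treatment arm respectively, with a common standard deviation of 2". The target is "at least 80% power to detect these changes for both endpoints at the 0.025 level of significance", and the result is that "43 subjects per group will give us over 95% power to detect the expected difference in estrogen and 80% power" for testosterone.

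**The concern.** Under the protocol's own assumptions the estrogen test is almost certain to succeed, yet the 0.025 assigned to it is not reused once it has succeeded. Testosterone is the endpoint that sets the sample size, and it sits just above the target, so testing it at 0.025 whatever happens to estrogen may give up power that could be kept within the same overall error limit. The power figure also assumes 43 analysable patients in each arm. Under the fixed split, the loss of one patient per arm takes testosterone below 80%.

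**Working it through.** **Inputs (Protocol, Statistical Plan).**
- 43 per arm, so 84 degrees of freedom.
- Testosterone: difference 1.36, SD 2, standardised effect 1.36/2 = 0.68.
- Estrogen: difference 47, SD 36, standardised effect 47/36 = 1.306.
- Level: 0.025 per endpoint.
- Sidedness is not stated. I assume two-sided tests, because the aim is put as "The goal is to determine if there is a difference in the change in these values between the two groups" and because two-sided 0.025 reproduces the stated 80%. One-sided 0.025 gives about 88% (normal approximation) and does not.

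**Reproducing the protocol's figures.** The power of a two-sample t-test comes from the noncentral t distribution with noncentrality d × √(n/2).
- Testosterone: 0.68 × √(43/2) = 3.153; critical value at two-sided 0.025 is 2.282; power 80.6% (normal approximation 81.9%).
- Estrogen: 1.306 × √(43/2) = 6.054; same critical value; power 99.99%.

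Both agree with the protocol's statements of 80% and over 95%.

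**Testosterone under Holm.** Holm rejects testosterone if its p-value is at most 0.025, or if it is at most 0.05 and the estrogen p-value is at most 0.025. With estrogen power at 99.99%, testosterone is in effect tested at 0.05.
- Critical value at two-sided 0.05 is 1.989; noncentrality is again 3.153; power 87.6%.
- Gain: 87.6 − 80.6 = 7.0 points (normal approximation 88.4 − 81.9 = 6.5).
- Simulation with 400,000 replicates and endpoint correlations of −0.3, 0, 0.3, 0.5 and 0.8 gives 87.6% to 87.7% throughout.
- With no effect on either endpoint, the simulated familywise error of Holm is 0.041 to 0.050 over the same correlations.

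**Dependence on the estrogen effect.** The extra rejections are those with a testosterone p-value between 0.025 and 0.05 in trials where estrogen succeeds, so the gain shrinks as estrogen power falls. Testosterone effect held at 0.68, correlation 0.3, 43 per arm (simulated):

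| True standardised estrogen effect | Estrogen power at 0.025 | Testosterone, fixed split | Testosterone, Holm | Gain (points) |
|---|---|---|---|---|
| 1.306 (planned) | 99.99% | 80.6% | 87.6% | 7.0 |
| 1.0 | 99.0% | 80.6% | 87.5% | 6.9 |
| 0.68 | 80.6% | 80.6% | 85.7% | 5.1 |
| 0.5 | 51.7% | 80.6% | 83.4% | 2.8 |
| 0.25 | 13.6% | 80.6% | 81.1% | 0.5 |
| 0 | 2.5% | 80.7% | 80.9% | 0.2 |

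**Fewer evaluable patients.** Testosterone power by noncentral t, with the planned estrogen effect:

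| Evaluable per arm | Fixed 0.025 | Holm (0.05 after estrogen) |
|---|---|---|
| 43 | 80.6% | 87.6% |
| 42 | 79.6% | 86.9% |
| 39 | 76.2% | 84.2% |
| 37 | 73.6% | 82.3% |
| 35 | 70.9% | 80.1% |

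Estrogen power at 0.025 is still 99.9% at 35 per arm. Going from 43 to 35 is a loss of 8/43 = 18.6%, and it uses up the whole gain.

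**The case against.** The strongest reply is that nothing here is wrong. The protocol sets an 80% target at 0.025, chooses a sample size that meets it, and uses the same level in the power and the analysis text. That stands in full. A reader might infer from the 7-point figure that the trial is underpowered or its multiplicity control faulty; the documents support neither.

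A second reply is that the fixed split does buy some error control, and this also stands. Both methods cap the familywise error at 0.05, but if estrogen responds as planned and testosterone does not, the fixed split makes a false testosterone claim 2.5% of the time and Holm 5.0%. The protocol's own background makes that case plausible: its Introduction cites a randomized soymilk study in which estrone fell and androgens did not, and its Study Design rationale cites two soymilk studies without a testosterone effect and a pilot with only a trend. It would therefore be too strong to say that the split costs power with nothing in return. It returns nothing in the familywise bound, but it does keep a stricter level for testosterone alone.

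Third, the 7 points rest on an estrogen effect taken from a pilot that, according to the Patient Accrual section, enrolled 13 patients. This too is fair, and the gain has to be quoted as a range. It does not reverse the comparison, because Holm rejects whatever the fixed split rejects, whatever the true effects are.

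Finally, fixed 0.025 tests pair directly with simultaneous 97.5% confidence intervals, and Holm has no equally simple counterpart. For a biomarker trial, where the size of the change is of interest, this is a real but small disadvantage.

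**Conclusion.** The point holds as an inexpensive improvement. The 0.025/0.025 split is valid and meets its target, but Holm is at least as powerful in every case at the same familywise 0.05. The gain for testosterone is roughly 0 to 7 points according to the true estrogen effect, and 7.0 points (80.6% to 87.6%) on the protocol's planning values.

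These figures assume two-sided tests, the protocol's testosterone effect and SD, 43 evaluable patients per arm, and a family made up only of the two Aim 1 primary endpoints. A reader might take 87.6% power and tolerance of about 18% data loss as joint benefits. They are alternatives: at 35 per arm the power is back to 80.1%, and that too depends on estrogen succeeding.

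**What to change.** In the Statistical Plan, replace the two fixed tests at 0.025 by Holm's procedure over total estrogen and testosterone: compare the smaller p-value with 0.025 and, if it is significant, the other with 0.05. Make the change in both the sample-size and the analysis text, and before unblinding. State that the tests are two-sided.

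Keep 86 patients. Give testosterone power as about 87.6% if the planned estrogen effect holds, with the gain over the fixed split shown as roughly 0 to 7 points. If the sponsor would rather use the gain as an allowance for missing data, say that about 35 evaluable per arm gives 80% under the same condition, and do not claim the higher power as well.

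The cost is one sentence in each of the two places and no change to endpoints, visits or sample size. The text should acknowledge that the testosterone-specific error rate can reach 5% when only estrogen responds. The Bonferroni 97.5% intervals can still be reported for description, noting that they will not always agree with the Holm decision. A sponsor who wants the stricter level for testosterone in its own right can keep the fixed split and give that reason.

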# Experimental Design:

# This will be a two-arm randomized study comparing a placebo control arm to supplementation with a commercial soy supplement. The time of initial biopsy to the time the surgery scheduled is typically 2-4 weeks in normal setting. Patients will be treated for a minimum of two weeks and continue treatment until the time of their prostatectomy. A total of 86 patients will be randomized (43 patients/arm).

Supplementation with Soy Isoflavones:

Dose Levels:

Dose 0: No soy (Placebo).

Dose 1: Four Capsules Twice Daily (240 mg of total isoflavones).

Treatment: The commercial soy supplement to be used is *Flav-Ein* (3B’s LTD, Lexena, Kansas)*.* This product was chosen because it is a pure soy extract and the individual concentration of each soy isoflavone is closely equivalent to a soy-based diet. It is supplied in capsular form. Each capsule contains 560 mg of pure soybean extract and 100mg of a non-soy legume (see appendix). Each capsule contains approximately 30mg of total isoflavones. The placebo will consist of an equivalent capsule with only the 100mg legume additive and no soy supplement.

1. ELIGIBILITY/EXCLUSION CRITERIA:

All patients must meet the following eligibility and exclusion criteria:

1. Histologically proven adenocarcinoma of the prostate.
2. Surgical candidate for radical prostatectomy.
3. During time of study period, patients must agree not to take any new vitamin supplementation or herbal remedy.
4. Must not be receiving concurrent chemotherapy, radiation or hormonal therapy.
5. No history of prior allergy and intolerability to soy-based products.
6. Must not have been taking any soy supplementation or soy isoflavones within 90 days prior to study enrollment.
7. Must be able to safely be on replacement for period of at least two weeks prior to the scheduled prostatectomy.
8. All patients must have been informed of the investigational natures of this study and must sign and give written informed consent in accordance with institutional and federal guidelines.
9. **STUDY CALENDAR**

| REQUIRED  STUDIES | Study Enrollment | Two Weeks | Preprostatectomy |
| --- | --- | --- | --- |
|  |  |  |  |
| EXAM |  |  |  |
| History/PE | X | X | X |
| Weight | X | X | X |
| PS | X | X | X |
| Toxicity | X | X | X |
|  |  |  |  |
| SERUM# |  |  |  |
| PSA | X | X | X |
| Estrogen(total) | X | X | X |
| Estradiol | X | X | X |
| Testosterone | X | X | X |
| DHT | X | X | X |
| SHBG | X | X | X |
| IGF-1 | X | X |  |

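### The primary test of change in estrogen and testosterone ignores the baseline values already collected; it is valid, but gives up some power for testosterone, the endpoint that sets the sample size

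*Protocol*

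**What the plan says.** The Statistical Plan names the endpoints: "Two primary endpoints for specific aim 1 are total serum estrogen and testosterone". On the level it says: "Each of these endpoints will be tested at the 0.025 level of significance". The confirmatory method follows under the Protocol's own Statistical Analysis Plan heading: "We will then compare the change in each of these endpoints using a two-sample t-test, at the 0.025 level of significance".

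The other serum endpoints get a similar comparison at 0.05. For ER-α and ER-β, the aim 2 primary endpoints, the text reads: "Similar analyses to what was used for specific aim 1 will be applied to these endpoints as well at the 0.05 level of significance".

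The only models with baseline terms are general linear models. They are labelled exploratory and are meant to find baseline characteristics that predict change, with treatment in the model. They do not replace or adjust the primary test.

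Baselines are available. Specific Aim 1, the Study Calendar and the laboratory section of Tissue and Serum Collection all place total estrogen and testosterone at enrollment, at two weeks and before prostatectomy.

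The trial is sized on the same t-test. For testosterone the assumption is "serum testosterone reduction will be 0 and 1.36 for the control and treatment arm respectively, with a common standard deviation of 2", and the stated result is that "43 subjects per group will give us over 95% power to detect the expected difference in estrogen and 80% power" for testosterone.

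**The concern.** Comparing raw change amounts to fixing the regression slope of follow-up on baseline at 1. When the true slope is below 1, patients who start high tend to fall and patients who start low tend to rise. Change is then negatively related to baseline. Part of its variance could be explained by a value already in the database, and a chance baseline difference between the arms feeds into the estimated effect in that particular trial. ANCOVA estimates the slope instead of fixing it.

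What is at stake is precision for testosterone. It sets the number of patients, and 43 per arm is the smallest number that reaches the 80% target with the planned test. The sample size section shows no allowance for patients without evaluable data.

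**Working it through.** **Inputs from the Statistical Plan.** Testosterone: difference 1.36, SD 2, read as the SD of the reduction. Estrogen: difference 47, SD 36. There are 43 patients per arm and alpha is 0.025 per endpoint. Sidedness is not stated; two-sided reproduces the stated power, whereas one-sided 0.025 would give 88.4% for testosterone (normal approximation).

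**Step 1: reproduce the stated power.** For the two-sample t-test with 84 df, the noncentrality is difference / (SD × √(2/43)), with √(2/43) = 0.2157. The two-sided critical value is 2.282.

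- Testosterone: 1.36 / (2 × 0.2157) = 3.153; power 80.6%.
- Estrogen: 47 / (36 × 0.2157) = 6.05; power about 99.99%.

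Both stated figures hold. For testosterone, the t-test gives 79.6% at 42 per arm, 78.5% at 41 and 76.2% at 39.

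**Step 2: effect of adjusting for baseline.** Let σ² be the variance at each time, assumed equal, and ρ the baseline to follow-up correlation.

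- Variance of change: 2σ²(1 − ρ)
- ANCOVA residual variance: σ²(1 − ρ²)
- Ratio: (1 + ρ)/2

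With the change SD held at 2, the ANCOVA residual SD is 2 × √((1 + ρ)/2). I charged ANCOVA one degree of freedom (83 df) and a chance-imbalance factor of √(1 + 1/81) on the SD. Example for ρ = 0.5: the SD is 2 × √0.75 = 1.732, inflated to 1.743; the noncentrality is 1.36 / (1.743 × 0.2157) = 3.62; power is 90.7%.

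**Step 3: range.** The Protocol gives no ρ, so every row below is an assumption.

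| ρ (assumed) | Residual SD | Testosterone power, 43 per arm | Per-arm n for 80% |
|---|---|---|---|
| 0.3 | 1.612 | 0.9437 | 29 |
| 0.5 | 1.732 | 0.9069 | 33 |
| 0.7 | 1.844 | 0.8656 | 37 |
| 0.8 | 1.897 | 0.8441 | 39 |
| 0.9 | 1.949 | 0.8225 | 41 |
| 0.95 | 1.975 | 0.8117 | 42 |
| t-test on change | 2.000 | 0.8063 | 43 |

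At ρ = 0.99 ANCOVA gives 80.3%, slightly below the t-test.

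**Step 4: without the equal-variance assumption.** If r is the correlation between change and baseline, the residual variance is the change variance times 1 − r². Testosterone power is then 80.1% at r = 0, 80.5% at −0.1, 84.0% at −0.3 and 90.7% at −0.5. The value at r = 0 is the worst case: 80.6% − 80.1% = 0.5 point lost.

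**Step 5: estrogen.** Power is about 99.99% by either method across this range.

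**The case against.** The strongest reply is that nothing in the plan is wrong. A t-test on change is unbiased under the planned randomization, the stated goal is a difference in change, the trial is sized on the same test, and the power reproduces. All of this stands. A reader might infer that the primary test is invalid, that the power statement is mistaken, or that the design misses its own target. The documents support none of these.

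A second reply is that the gain rests on an undocumented correlation and on equal variances. This also stands. If the slope (ρ times the follow-up SD over the baseline SD) equals 1, there is no gain. It would therefore be too strong to say that ANCOVA is always more precise, that it costs nothing, or that it would save a given share of patients.

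A third reply is that the scope is narrow. Estrogen has nothing material to gain. For ER-α and ER-β the Protocol gives no SD or power, the baseline is a needle biopsy and the follow-up a prostatectomy specimen, so the equal-variance formula cannot simply be carried over. A reader might extend the testosterone figures to the receptors or the other serum markers; nothing supports that.

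Finally, the exploratory linear models may already yield the adjusted estimate. A model of change on arm and the marker's own baseline gives the same treatment estimate as ANCOVA on the follow-up value. But the text does not say that the marker's own baseline will be included, and an exploratory model cannot carry the confirmatory conclusion.

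**Conclusion.** The point holds as a modest loss of efficiency in a valid and coherent plan. It matters for testosterone only. At an assumed ρ of 0.5 to 0.8, the primary test gives up about 4 to 10 points of power (84.4% to 90.7%, against 80.6%). That is the equivalent of 4 to 10 patients per arm at the 80% target. The gain is 0.5 point at ρ = 0.95 (81.2%) and essentially nil close to 1. If baseline does not predict change, ANCOVA costs about half a point. These figures rest on the Protocol's difference of 1.36 and change SD of 2, two-sided testing at 0.025, and equal baseline and follow-up variances.

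The balance favors adjustment because the downside is small and bounded, while the planned test has almost no margin at 43 per arm.

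**What to change.** Before unblinding, replace the primary comparison for each aim 1 endpoint with an ANCOVA: post-treatment value (or change) on arm plus the same marker's baseline, at alpha 0.025. Keep the total at 86; a smaller sample should not be planned on an unknown correlation. Keep the change-score t-test as a sensitivity analysis.

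The same model can be used for the other serum endpoints and for ER-α and ER-β at their stated level, without claiming a known gain. For the receptors, the text should acknowledge that baseline and follow-up come from different kinds of specimen.

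The cost is a short change of wording and one degree of freedom. No new patients, visits or assays are needed.

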11. HUMAN SUBJECTS PROTECTION 13-14
12. REFERENCES 15-18

Appendix 1: Informed Consent

Appendix 2: NCI Common Terminology Criteria for Adverse Events (Version 3.0)

1. OBJECTIVES

Commercial soy products have been widely promoted and are consumed by a significant number of patients, either in an effort to prevent or treat prostate cancer. The mechanism of action of these products, appropriate dose, degree of benefit and safety profile, however, remains unknown.1 Our central hypothesis is that soy supplements do have beneficial effects in decreasing prostate cancer proliferation and development and, that this effect is related to the phytoestrogenic activity of the soy isoflavones. We propose to examine the effect of a commercially available isoflavone containing soy-based product in patients with adenocarcinoma of the prostate. The patient population to be studied is patients who are scheduled to undergo a radical prostatectomy as the primary treatment for their prostate cancer. This patient population is chosen because the soy isoflavones are more likely to have a benefit early in prostate cancer development and the availability of tissue from prostatectomy specimens is ideal for study the soy effects. The proposed project is a randomized two-arm study comparing a commercial soy supplement to placebo. Specific aim 1 concerns the clinical protocol and specific aims 2&3 the basic science studies.

Specific Aim 1: To assess the effect of soy supplementation on endogenous hormone levels and serum prostate specific antigen. Our hypothesis is that soy supplementation and genistein will decrease serum estrogen and androgen levels, and that these changes will correlate with the molecular effects evaluated in specific aims #2 and #3. Serum levels of testosterone, dihydrotestosterone (DHT), total estrogen, estradiol, sex hormone binding globulin (SHBG), and prostate specific antigen (PSA) will be measured in all groups at the time of randomization (prior to soy supplementation), after two weeks of supplementation and prior to radical prostatectomy (completion of soy supplementation). Serum levels of genistein, insulin-like growth factor-1 (IGF-1) and insulin-like growth factor binding protein-3 (IGFBP-3) will be measured at randomization and after two weeks of supplementation.

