**Specific Aim 2: To assess the impact of soy supplementation on the estrogen receptor (ER) including ER alpha and ER beta.** **Our hypothesis is that soy isoflavones decrease prostate cancer proliferation by exerting antiestrogenic effects on ER- dependant mechanisms, with a resultant down regulation of ER- expression.** Proposed experiments will examine the direct effect of soy isoflavones on estrogen receptor expression. This effect will be compared with the resultant changes in tumor cell apoptosis and proliferation. Specific experimental approaches include: (i) measurement of ER- and ER-ß expression in needle biopsy specimens (pre-soy) and from the radical prostatectomy specimens (post-soy), (ii) measurement of apoptotic cell death using the TUNEL assay and (iii) measurement of proliferation indicesusing PCNA immunohistochemical analyses. Receptor expression levels and degree of apoptosis will be compared between the two groups and will be correlated with patient specific profiles that will include pretreatment tumor stage, PSA, and Gleason’s score.

**Specific Aim 3: To determine the impact of soy isoflavones on cell cycle regulation and associated gene expression. Our hypothesis is that soy isoflavone modulation of the estrogen receptor results in signals that eventually deregulate cell cycle regulatory proteins in the target cells, resulting in the inhibition of tumor proliferation and apoptotic cell death.**  Proposed studies will evaluate effects of soy isoflavones on the gene expression in both the primary prostate tumor and the adjacent non-malignant gland. Specifically, we will: (i) measure cell division cycle-2 kinase (cdc-2) and phosphorylated cdc-2, (ii) evaluate the status of genes essential for cell cycle regulation using cDNA microarray analyses and (iii) further characterize changes in gene expression using Northern and Western Blots. Fresh tumor samples and an area of adjacent normal gland will be obtained on randomized patients. These results will be correlated with the serum hormonal changes identified in specific aim 1 and the estrogen receptor level expression changes identified in specific aim 2.

1. **INTRODUCTION**

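### The exploratory Pearson correlation of biomarker changes has no control for arm, so markers that soy shifts tend to correlate through the arm difference alone

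*Protocol*

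**What the plan says.** In the protocol's Statistical Plan, under Statistical Analysis Plan, the two primary serum endpoints are compared between arms by t-tests on change. A secondary paragraph follows. It begins "In an exploratory manner, we will use general linear models", and these models ask whether "baseline characteristics are predictive of change in these variables while controlling for treatment". The next sentence adds Pearson's "correlation to determine if changes in the biomarkers are correlated with one another". That sentence mentions neither treatment nor separate analyses by arm, and it sets no significance level. The paragraph then says that the two estrogen-receptor endpoints of Aim 2 will be analysed in a similar way.

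The Objectives section shows what the correlations are for. The Aim 1 hypothesis is that soy lowers serum hormones and that "these changes will correlate with the molecular effects evaluated in specific aims #2 and #3". For the gene-expression work of Aim 3 it says "These results will be correlated with the serum hormonal changes identified in specific aim 1", and it adds the receptor changes of Aim 2. Neither aim names a statistic for this.

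The planning effects are under Sample Size and Power: "total serum estrogen reductions will be 0 and 47 in the control and treatment arm respectively, with a common standard deviation of 36", and "serum testosterone reduction will be 0 and 1.36 for the control and treatment arm respectively, with a common standard deviation of 2".

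**The concern.** In a two-arm trial, arm is a common cause of every marker that the treatment moves. If changes are pooled over arms with different means, part of the correlation between two markers is the arm contrast itself. The coefficient then mixes two questions: whether soy moved both markers on average, and whether the man with the larger hormone change also has the larger molecular change. The t-tests already answer the first. Only the second adds evidence on mechanism, which is what the Aim 1 hypothesis is about.

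The artefact needs both markers to shift, so it arises when the trial works as planned. If the two shifts have opposite signs, the artefact is negative and can hide or reverse a genuine positive association.

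**Working it through.** **Inputs.** From Sample Size and Power: estrogen reduction 0 vs 47 with SD 36, so d1 = 47/36 = 1.306; testosterone reduction 0 vs 1.36 with SD 2, so d2 = 1.36/2 = 0.68; 43 per arm, N = 86. My assumptions: zero within-arm correlation, normal changes with equal variance in both arms, complete data, and a two-sided 0.05 threshold for the correlation.

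**The plan's own figures.** A two-sample t-test at two-sided 0.025 (sidedness is not stated) with 43 per arm has 99.99% power for estrogen and 80.6% for testosterone (exact noncentral t, 84 df). The stated figures of over 95% and 80% are reproduced, so these effect sizes are the ones the plan used.

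**Correlation created by pooling.** In SD units with 1:1 allocation, the arm indicator has variance 1/4. Pooling therefore adds d1·d2/4 to the covariance and d²/4 to each variance:

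r = (d1·d2/4) / √[(1 + d1²/4)(1 + d2²/4)]

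For estrogen and testosterone:
- numerator: 1.306 × 0.68 / 4 = 0.222
- denominator: √(1.426 × 1.116) = 1.261
- r = 0.222 / 1.261 = 0.176

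**How often it reaches p<0.05.** Each row is 40,000 simulated trials of 43 + 43 with no within-arm association. The partial correlation removes the arm means and has 86 − 3 = 83 df.

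| Shift of marker 1 (SD) | Shift of marker 2 (SD) | Induced r | Pooled Pearson, p<0.05 | Partial given arm, p<0.05 |
|---|---|---|---|---|
| 1.306 (estrogen) | 0.68 (testosterone) | 0.18 | 38% | 5% |
| 1.306 | 1.306 (assumed) | 0.30 | 83% | 5% |
| 1.306 | 0.5 (assumed) | 0.13 | 23% | 5% |
| 1.306 | 0.3 (assumed) | 0.08 | 12% | 5% |
| 0.68 | 0.68 (assumed) | 0.10 | 16% | 5% |
| 1.306 or 0.68 | 0 | 0 | 5% | 5% |
| 0 | 0 | 0 | 5% | 5% |

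A hand check of the first row by Fisher's z: atanh(0.176) × √83 = 0.178 × 9.11 = 1.62, and P(Z > 1.96 − 1.62) = P(Z > 0.34) ≈ 0.37, close to the simulated 38%.

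Only the first row rests wholly on the protocol's effects. The rows marked as assumed show a range, because the protocol gives no effect size for receptor expression, apoptosis, proliferation or gene expression. If both shifts are small the artefact nearly vanishes: at 0.3 SD each, r = 0.0225/1.0225 = 0.02.

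**Opposite shifts.** With a within-arm correlation ρ, the pooled covariance is ρ + d1·d2/4. If soy moved two markers by 1.306 and 0.68 SD in opposite directions, the second term would be −0.222. A genuine within-arm correlation of about +0.22 would then average out to zero in the pooled coefficient.

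**The case against.** The strongest reply is that pooling is inferred. The protocol does not say that the arms are combined, a within-arm Pearson correlation fits the same words, and such detail is often left to a statistical analysis plan, which is not at hand. That stands in part. Still, the protocol names treatment control for one analysis and omits it for the next, and the method it names does not suit its purpose under the natural reading.

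Second, the analysis is exploratory and has no significance level attached. This stands: the rejection rates describe what follows if someone reads p<0.05 as notable, not an error rate that the protocol undertakes to control. Exploratory status does not change which question the coefficient answers.

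Third, a correlation that arises because soy moves both markers is a real marginal association and agrees with the Aim 1 hypothesis. That is true. The 38% counts as false positives only if the target is association beyond the arm difference. But that is the only part the t-tests do not already supply.

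A reader might go further and infer that any two markers soy shifts will look linked, so that the mechanism hypothesis would be confirmed with nothing behind it. The figures do not support that. With the planning effects the induced r is modest and misses p<0.05 in about 62% of trials (100 − 38), and no confirmatory test is planned here. A reader might also infer that Aim 3 is to be analysed by unadjusted Pearson correlation. The protocol states that intention without naming a statistic.

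**Conclusion.** The point holds as a weakness of an exploratory analysis, worth correcting. Under the natural pooled reading, two markers that soy shifts tend to correlate through the arm difference. For the two primary hormones, with the protocol's planning effects and no within-arm link, the expected r is about 0.18 and p<0.05 occurs in about 38% of trials, against about 5% after adjustment for arm.

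For hormone against tissue marker, the comparison that matters most for mechanism, the size is unknown. A 1.31 SD shift paired with an assumed 0.3 to 1.31 SD gives about 12% to 83%. Two smaller shifts give less, and the rate is 5% when at most one marker moves. The primary t-tests, sample size and power are untouched.

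**What to change.** In the Statistical Analysis Plan paragraph, replace the plain Pearson correlation with the partial Pearson correlation of changes controlling for arm (83 df with all 86 patients), and report the two within-arm correlations beside it. Say that the same approach applies to the estrogen-receptor endpoints of Aim 2 and to any correlation of Aim 3 results with hormone changes. If within-arm analysis was always intended, say so.

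The cost is a sentence or two of text and one degree of freedom. No new data are needed, and the primary analyses do not change.
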